## Abstract

**Supplementary Information:**

The online version contains supplementary material available at 10.1186/s13063-023-07330-z.

## Introduction

### Background and rationale

The placement of an endotracheal tube for children with acute or critical illness is a low-frequency and high-risk procedure, associated with high rates of first-attempt failure and adverse events, including hypoxaemia [1]. To reduce the frequency of these adverse events, the provision of oxygen to the patient during the apnoeic phase of intubation has been proposed as a method to prolong the time available for the operator to insert the endotracheal tube, prior to the onset of hypoxaemia [2]. However, there are limited data from randomised controlled trials to validate the efficacy of this technique in children.

The technique known as transnasal humidified rapid insufflation ventilatory exchange (THRIVE) uses high oxygen flow rates (approximately 2 L/kg/min) delivered through nasal cannulae during apnoea. It has been shown to at least double the amount of time available for safe intubation in healthy children undergoing elective surgery [3]. The technique and its application in real time have not previously been studied in acutely ill or injured children presenting to the emergency department or admitted to an intensive care unit.

### Intervention

A detailed description of the intervention is included in the previously published protocol paper [4]. In brief, eligible participants will be randomised to receive either standard care (control) or THRIVE during the apnoeic period of endotracheal intubation.

Participants randomised to standard care will be intubated according to site-specific guidelines or clinician preference, with no provision of apnoeic oxygen during the intubation. Those randomised to the THRIVE intervention will be administered high-flow oxygen through nasal cannula at a flow rate of approximately 2 L/kg/min. The intervention will be applied immediately after the mask or device used for preoxygenation is removed and before the laryngoscope is introduced into the mouth.

The intubation procedure will proceed according to standard hospital procedures and clinician preference, with study data continuously collected during the procedure.

### Objectives

The primary objective of the trial is to determine if the use of THRIVE reduces the frequency of oxygen desaturation and increases the frequency of first-attempt success without hypoxaemia in emergent intubation of children compared with standard practice. The secondary objectives of the study are to assess the impact of the use of THRIVE on the rate of adverse events, length of mechanical ventilation and length of stay in intensive care.

## Study methods

### Trial design

The Kids THRIVE trial is a multicentre, international, randomised controlled trial (RCT) in children less than 16 years old undergoing emergent intubation in either the intensive care unit or emergency department of participating hospitals. Participants will be randomised to receive either the THRIVE intervention or standard care (no apnoeic oxygenation) during their intubation. Further details can be found in the previously published protocol [4].

### Sample size

A conservative estimate of the primary outcome of hypoxaemia is set at 16%, following an unpublished 2016 audit of data from the Queensland Children’s Hospital, which we found was comparable to a published report [1]. Assuming a clinically relevant effect size of a 50% reduction in the proportion of desaturation events from 16 to 8%, along with a type I error of 0.025 (adjusting for two primary outcomes using Bonferroni’s correction) and power of 90%, 816 intubation encounters in total are required. Successful first-attempt intubation, the second primary outcome, assumes an absolute increase from 60 to 80%, requiring 258 intubation encounters. Allowing for 15% attrition, the total sample size that will satisfy both primary outcome measures is 960 intubation encounters. An attrition rate of 15% was selected based on the assumption that a proportion of patients enrolled will have a clinical deterioration, or other clinical events, during a high-stress procedure leading to the inability to deliver the intervention or collect the outcome data required for the study.

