### Statistical principles

The primary analysis will be conducted based on the intention-to-treat principle. Specifically, each randomised intubation encounter will be analysed based on the allocated treatment group, independent of compliance with the treatment delivered.

A per-protocol analysis including all intubation attempts where a study therapy was commenced (regardless of whether it was the therapy that was randomised) will also be undertaken and reported in the supplementary material.

The unit of analysis for most outcomes is the intubation encounter. If patients are required to be intubated more than once, they can be re-enrolled and re-randomised, theoretically receiving different study interventions for each intubation attempt within a single admission. For secondary outcomes relating to admission (i.e. ventilator-free days, length of ICU and hospital stay and death), only those patients with one enrolment per admission will be included in the primary and per-protocol analyses.

Statistical tests will be two-sided applying a statistical significance level of 0.05, although the primary outcomes will be analysed at a level of 0.025 (applying Bonferroni’s correction). We will not apply a formal correction for multiple testing to any of the subgroup analyses, sensitivity analyses or to the secondary outcomes. We will ensure conclusions drawn as a result of analyses are interpreted with deference to multiple comparisons.

If there is more than 10% of data missing for the primary outcomes, a sensitivity analysis using multiple imputation will be undertaken.

Continuous variables will be assessed for normality; this will be undertaken using visual inspection of histograms and *Q*-*Q* plots.

Descriptive statistics will be used when summarising variables; frequencies (percentages) for discrete variables, mean and standard deviation (SD) for normally distributed continuous variables, or, if continuous variables are non-normally distributed, median with interquartile range (IQR).

Subgroup analyses will be executed regardless of any potential treatment effect on the primary or secondary outcomes in the main cohort.

Changes to the analysis plan by the investigators effective after the publication of this SAP will be declared as such.

The statistical analysis will be undertaken using StataSE version 17 (StataCorp Pty Ltd., College Station, TX).

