#### Missing data

The primary outcome for this study is recorded by two methods, paper CRF and video recording, as such it is expected that there will be very few participants with missing primary outcome data. Where the data is not recorded on either the paper CRF or video, the medical record will be used to source the required data. As such, multiple imputation will only be undertaken if > 10% of the primary outcome data is unavailable and reported as sensitivity analysis. The fully conditional specification will be used for imputation; the imputation model will include randomised treatment arm, study site and the stratification variable. Ten sets of imputed data will be created using the methods described for the primary outcome. A pooled common effect estimate and 95% confidence interval will be generated from the imputed datasets.

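### The 15% attrition allowance counts undelivered interventions as lost encounters, but intention-to-treat keeps them, so 960 encounters give about 83% to 90% power for hypoxaemia depending on an unstated split

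*SAP article*

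**What the plan says.** All references are to the SAP article.

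- **Sample size, rate and effect:** "A conservative estimate of the primary outcome of hypoxaemia is set at 16"%, with a target of "a 50% reduction in the proportion of desaturation events from 16 to 8"%. 
- **Sample size, error rates:** a "type I error of 0.025" for each of the two primary outcomes, and "power of 90%, 816 intubation encounters in total are required". First-attempt success (60% to 80%) needs 258. Hypoxaemia therefore sets the size.
- **Sample size, attrition:** 15% is allowed for, giving 960. The reason given is deterioration or other clinical events "leading to the inability to deliver the intervention or collect the outcome data required for the study". The two causes are joined by one word, and the 15% is not split between them.
- **Statistical principles:** encounters are analysed in the allocated group, "independent of compliance with the treatment delivered". A per-protocol analysis goes to the supplement. On sidedness: "Statistical tests will be two-sided applying a statistical significance level of 0.05", with 0.025 for the primary outcomes.
- **Missing data:** the outcome is captured on paper form and video, with the medical record as fallback, so "it is expected that there will be very few participants with missing primary outcome data".

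**The concern.** Dividing by one minus the attrition rate is right for encounters that contribute no outcome: the analysed number shrinks and the effect among those left is unchanged. It is not right for encounters that are analysed but did not receive the allocated treatment. Those leave the number intact and shrink the difference between arms.

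The Sample size section puts both kinds of event into one 15% and treats all of it as lost numbers. The intention-to-treat rule makes the non-delivery part a dilution problem. The Missing data section suggests that the other part, missing outcomes, will be small.

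At stake is the stated 90% power for the outcome that determines the sample size. If hypoxaemia shows no significant difference, readers will judge that result against 90% power, which the design may not have under its own analysis rule.

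**Working it through.** **Inputs from the SAP article.** Control risk 16%, THRIVE risk 8%, alpha 0.025 per primary outcome, power 90%, attrition 15%, total 960 (Sample size); two-sided tests (Statistical principles); 1:1 allocation (Randomisation), hence 480 per arm.

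**Assumptions not in the document.** (a) The 8% is the risk when THRIVE is delivered. (b) A THRIVE encounter without delivery has the 16% control risk. (c) Missing outcomes fall equally on both arms.

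**Step 1: reproduce the plan's figures.** Two-proportion formula, pooled variance under the null, no continuity correction, with z(0.9875) = 2.2414, z(0.90) = 1.2816 and p̄ = (p1 + p2)/2:

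n per arm = [2.2414·√(2p̄(1−p̄)) + 1.2816·√(p1(1−p1) + p2(1−p2))]² / (p1 − p2)²

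- Hypoxaemia, 0.16 v 0.08: n = 407.3, so 408 per arm, 816 in total.
- First-attempt success, 0.60 v 0.80: n = 128.04, so 129 per arm, 258 in total.
- 816 / 0.85 = 960.

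All three match the plan exactly.

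**Step 2: dilute the effect.** Let u be the share of randomised encounters with no delivery but a recorded outcome, and 0.15 − u the share with a missing outcome.

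- Analysed per arm: n = 480 × (1 − (0.15 − u)).
- Undelivered share of the analysed THRIVE encounters: f = u / (1 − (0.15 − u)).
- Diluted THRIVE risk: p2 = 0.08(1 − f) + 0.16f = 0.08 + 0.08f.
- Power = Φ{[(0.16 − p2) − 2.2414·√(2p̄(1−p̄)/n)] / √[(0.16·0.84 + p2(1−p2))/n]}.

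| Non-delivery | Missing outcome | n per arm | f | p2 | Power |
|---|---|---|---|---|---|
| 0 | 15 points | 408 | 0 | 8.00% | 90.1% |
| 5 points | 10 points | 432 | 5/90 = 5.6% | 8.44% | 87.6% |
| 10 points | 5 points | 456 | 10/95 = 10.5% | 8.84% | 85.1% |
| 15 points | 0 | 480 | 15% | 9.20% | 82.6% |

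In the last row the numerator is 0.068 − 2.2414 × 0.02142 = 0.01999 and the denominator is 0.02131, so z = 0.938 and power is 82.6%. The difference between arms has fallen from 8.0 to 6.8 points. The same formula would need 589 per arm (1,178 in total) for 90% power in that row.

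**Step 3: the other primary outcome.** With 15% non-delivery, first-attempt success is 60% v 0.85 × 80% + 0.15 × 60% = 77%. At 480 per arm, power is above 99.9%.

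**Step 4: sensitivity to assumption (b).** Take all 15% as non-delivery, hold the overall control risk at 16% and halve the risk among delivered encounters. If undelivered encounters carry a risk of 20%, 25% or 30% in both arms, power is about 78%, 72% or 65%. These risks are illustrative; the document gives no figure.

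**The case against.** **The 16% to 8% difference may already be an intention-to-treat target.** The section presents it as a clinically relevant difference and does not say it applies only where THRIVE is delivered. On that reading there is no dilution to correct, and with all 960 analysed (480 per arm, 16% v 8%) power is about 94%. This stands as a possible reading. But non-delivery would then have no place in the attrition allowance, so the paragraph is inconsistent either way.

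**The split is unknown.** The expectation of few missing outcomes carries no figure. It could also mean that 15% is simply generous and total losses will be smaller. Encounters excluded for lack of consent (Withdrawal section) are true losses that dividing by 0.85 would cover, although the Sample size section does not give consent as a reason. This stands: the document does not prove that most of the 15% is non-delivery.

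**The control rate is described as conservative.** With a halved risk and full 15% non-delivery, power is about 88% at an 18% control rate and 92% at 20%. This also stands, but the stated 90% is tied to 16%.

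**A reader might infer that the trial has 83% power at most, or far less.** The document does not support that. Under the base assumptions 83% is the bottom of the range, and the lower values need a risk in undelivered encounters that appears nowhere in it.

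**The practical effect is limited.** The arithmetic is correct, no analysis or decision rule changes, and odds ratios will be reported with 95% confidence intervals, from which a null result can be judged. That limits the weight of the point but does not make the stated power right.

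**Conclusion.** The point holds as an inconsistency between the sample size justification and the analysis rule, not as an arithmetic error. Non-delivery is counted as attrition, yet those encounters stay in the primary analysis whenever their outcome is recorded.

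If 16% to 8% is a full-delivery effect and undelivered THRIVE encounters have the control risk, power for hypoxaemia at 960 is between about 83% and 90%, according to how the 15% divides. The stated 90% holds only if the whole 15% is missing outcomes. The plan's own expectation of few missing outcomes makes the lower end the more plausible. Power would fall below 83% if undelivered encounters are at higher risk. That is conceivable, because the section links the 15% to clinical deterioration, but the document does not allow it to be quantified. The first-attempt outcome is not materially affected.

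**What to change.** In the Sample size section:

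1. Separate the 15% into an allowance for missing outcomes and an allowance for non-delivery with a recorded outcome. Apply the division by one minus the rate only to the first.
2. State whether 16% to 8% is the difference expected under intention to treat or under full delivery.
3. If it is a full-delivery effect, restate the intention-to-treat power for hypoxaemia at 960 encounters as about 83% to 90% depending on the split, and give the assumed risk in undelivered encounters.

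This costs one paragraph of text. Enrolment and the analysis stay as they are. The downside is that the stated power becomes less favourable.

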### Randomisation

A computer-generated randomisation sequence using block randomisation (block size = 10) with a 1:1 ratio and stratification by site, age (< 1 year, 1–7 years and > 7 years of age), then level of the intended first operator seniority (junior and senior medical officer) was developed. Randomisation is conducted using sequential, numbered, sealed, opaque envelopes, provided to each site. The use of a fixed block size is unlikely to reduce the allocation concealment as randomisation occurs by any member of the large clinical team, including when the research staff are not present outside of usual business hours. Thus, any person selecting the envelope is unlikely to be aware of the previous allocations in the block. After a patient has been screened and confirmed as eligible and the operator for the intubation has been determined, the enrolling clinician selects the next envelope to reveal the study randomisation for that intubation encounter.

### Interim analyses

An independent Data and Safety Monitoring Board (DSMB) has been convened for this study.

Interim analyses were pre-defined to assess the progress and safety of the trial after the primary outcome was known for 100 and 200 children. At the DSMB establishment meeting, the DSMB requested a modification to the interim analysis schedule to include a safety review at 100 patients, a safety and efficacy analysis at 300 patients and removal of the 200-patient review point. This was requested as the study was powered for one of the primary outcomes once outcomes were available for 300 children. The request was discussed and agreed upon by the trial steering committee and incorporated into the updated protocol. While no formal stopping rule was used, the DSMB could recommend ceasing the trial if there is a statistically significant difference (*p* < 0.001) in the primary outcome between the treatment groups overall or within pre-specified age subgroups, or in the case of serious adverse events. Cessation of the trial could also be recommended if there is equipment failure or recall, or if other evidence becomes available that would make continuing the trial unethical.

The blinded outcome information was presented to the DSMB by a pseudo-labelled treatment arm. No unblinding of the data was requested by the DSMB. The DSMB recommended the continuation of the trial with no protocol changes following a review of data and adverse events at both interim analyses.

### Timing of final analysis

The final analysis will be conducted after data entry and monitoring have been completed and the database is cleaned and closed.

### Data sources

Four data sources are being used for data collection:Clinical record: data from the patient’s hospital medical record including demographics, diagnosis, admission and intubation information.Paper case report form (CRF): source data including patient observations and intubation-specific details will be entered directly onto a paper CRF by a researcher or clinician during the intubation.Video of the intubation attempt/s: a video recording device has been provided to each site and placed in a location to obtain a full view of the intubating clinician and child’s face (additional information on this aspect previously published [4]). Where there is a discrepancy between manually recorded data and video data, the video-collected data will be used for analysis. Videos are stored locally and then uploaded to The University of Queensland (UQ) Research Data Manager (RDM).The Australian and New Zealand Paediatric Intensive Care Registry (ANZPICR): the ANZPICR identifier is collected for each patient admitted to a paediatric intensive care unit. These identifiers are provided to the ANZPICR who subsequently provide an extract containing information relating to diagnosis, demographic characteristics, start and stop times of mechanical ventilation episodes and outcomes.

Data from all four sources is collected and entered into the purpose-built study database developed in REDCap and hosted by UQ [5, 6], either by direct entry, paper record upload or import.

### Data monitoring

Data monitoring is being undertaken throughout the trial, based on a data monitoring plan devised by the study team. The data monitoring plan was developed in accordance with the ICH E6 (R2) Good Clinical Practice Guideline [7] and reflects the current best practice for data monitoring practices in investigator-initiated trials. Briefly, the data monitoring plan includes the following components:Data verification on all screening data items (i.e. inclusion and exclusion criteria) for every enrolled patient (utilising the clinical record)Data verification on the stratification used for randomisation and consent data items for every enrolled patient (utilising the clinical record, ANZPICR, paper CRF)Data verification on the data items related to the calculation of the primary and secondary outcomes for every enrolled patient (utilising the clinical record, ANZPICR, paper CRF, intubation video)Data verification on key data items relating to cohort descriptors on a random sample of 10% of enrolled patients from each site (utilising the clinical record, ANZPICR)Data verification on reported adverse events for every enrolled patient (utilising the clinical record, intubation video)Clinical record and intubation video review for every enrolled patient to determine if all adverse events and protocol deviations have been reported

The original study REDCap database was enhanced to facilitate the activities outlined in the data monitoring plan. Each site is being monitored by a research coordinator not involved with the recruitment at that site. This is being undertaken through a combination of on-site monitoring and remote monitoring using the institutional programme to share desktop computer screens, remote access to electronic medical records as well as via the upload of source documents to the RDM. Uploaded videos are watched by the independent monitor and the relevant data items extracted and compared to those entered. During the coronavirus disease 2019 pandemic (COVID-19), monitoring is primarily being undertaken using remote methods; however, on-site monitoring may still occur following the easing of COVID-19 restrictions. Each relevant data item is verified individually by comparing the entered value with the value in the source documentation. Where discrepancies are found, the site research coordinator and monitor meet to discuss and resolve the discrepancies. Once data monitoring is finalised, the patient’s REDCap data entry record is locked in preparation for analysis.

### Statistical principles

The primary analysis will be conducted based on the intention-to-treat principle. Specifically, each randomised intubation encounter will be analysed based on the allocated treatment group, independent of compliance with the treatment delivered.

A per-protocol analysis including all intubation attempts where a study therapy was commenced (regardless of whether it was the therapy that was randomised) will also be undertaken and reported in the supplementary material.

The unit of analysis for most outcomes is the intubation encounter. If patients are required to be intubated more than once, they can be re-enrolled and re-randomised, theoretically receiving different study interventions for each intubation attempt within a single admission. For secondary outcomes relating to admission (i.e. ventilator-free days, length of ICU and hospital stay and death), only those patients with one enrolment per admission will be included in the primary and per-protocol analyses.

Statistical tests will be two-sided applying a statistical significance level of 0.05, although the primary outcomes will be analysed at a level of 0.025 (applying Bonferroni’s correction). We will not apply a formal correction for multiple testing to any of the subgroup analyses, sensitivity analyses or to the secondary outcomes. We will ensure conclusions drawn as a result of analyses are interpreted with deference to multiple comparisons.

If there is more than 10% of data missing for the primary outcomes, a sensitivity analysis using multiple imputation will be undertaken.

Continuous variables will be assessed for normality; this will be undertaken using visual inspection of histograms and *Q*-*Q* plots.

Descriptive statistics will be used when summarising variables; frequencies (percentages) for discrete variables, mean and standard deviation (SD) for normally distributed continuous variables, or, if continuous variables are non-normally distributed, median with interquartile range (IQR).

Subgroup analyses will be executed regardless of any potential treatment effect on the primary or secondary outcomes in the main cohort.

Changes to the analysis plan by the investigators effective after the publication of this SAP will be declared as such.

The statistical analysis will be undertaken using StataSE version 17 (StataCorp Pty Ltd., College Station, TX).

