#### Analysis methods

##### Primary outcome measures

The primary outcome measures will be analysed using logistic regression adjusting for the treatment group and the stratification variables (age group, operator level) as fixed effects and site and patient as random effects (allowing for the same patient to be recruited more than once into the study). A model without adjustment for age group or operator level will also be reported. Unadjusted and adjusted odds ratios (ORs), 95% confidence intervals (CIs) and *p*-values for the adjusted model will be reported (Table 2). Assumptions of the models will be tested and reported on.

**Table 2 Tab2:** Intubation characteristics of participants enrolled in the Kids THRIVE trial

Characteristic	Standard care, *N* =	THRIVE, *N* =
**Intubation location,** *n (%)*		
Emergency department		
Paediatric intensive care		
Neonatal intensive care		
Others		

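### The set labelled per-protocol admits encounters given the non-allocated therapy and leaves its grouping open, so it is either as-treated or modified intention-to-treat (moderate; the primary analysis is unaffected)

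*SAP article*

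**What the plan says.** The Statistical principles section of the SAP article describes two analyses in succession. For the primary one, "each randomised intubation encounter will be analysed based on the allocated treatment group, independent of compliance with the treatment delivered"; both the set and the grouping are fixed. The second is a "per-protocol analysis including all intubation attempts where a study therapy was commenced (regardless of whether it was the therapy that was randomised", which "will also be undertaken and reported in the supplementary material". That sentence says which encounters enter, but not the arm in which they are counted.

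The same section carries the second analysis over to ventilator-free days, lengths of stay and death, where "only those patients with one enrolment per admission will be included in the primary and per-protocol analyses".

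Three other places bear on it:
- **Intervention:** THRIVE starts once the preoxygenation device comes off and before laryngoscopy. Standard care is local or clinician practice "with no provision of apnoeic oxygen during the intubation".
- **Sample size:** the 15% attrition allowance is justified partly by patients who deteriorate so that the intervention cannot be given.
- **Primary outcome measures:** the model is "logistic regression adjusting for the treatment group and the stratification variables (age group, operator level) as fixed effects", with site and patient as random effects.

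The list of planned appendix material names the per-protocol results and adds nothing to the definition.

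**The concern.** A per-protocol set is normally restricted to units treated as allocated. This definition waives that condition in so many words, so it states a rule and is not a detail left to the protocol. Because the grouping is not given, two analysts could follow the SAP faithfully and report different results under one label.

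Readers turn to a per-protocol result to judge the effect when the protocol is followed. That question is a live one here, because the plan itself expects deterioration to interfere with delivery. Under this definition the supplementary result could show an effect produced by who switched, could hide a real effect, or could repeat the ITT result and look like independent support for it.

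**Working it through.** **1. The plan's own figures.** The definition rests on no stated number, but the illustration in step 4 borrows the planning rates, so these were checked first. With pooled variance, two-sided alpha 0.025 and 90% power, 16% versus 8% needs 408 per arm (816 in total), and 60% versus 80% needs 129 per arm (258). Then 816 / (1 − 0.15) = 960. All three match the Sample size section. They are not affected by this point.

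**2. The two readings.**
- *Grouped by therapy received.* Encounters that switched are counted in the arm whose therapy they got. Switching linked to the child's condition is then confounded with treatment. The model holds treatment, age group, operator level, site and patient, and nothing on severity.
- *Grouped by allocation.* Encounters that switched stay in their randomised arm. Only those with no therapy commenced leave. This is a modified ITT set, and it equals the ITT set if none leave.

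Neither reading requires that the allocated therapy was received.

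**3. Where the entry condition is imprecise.** A THRIVE-allocated encounter in which THRIVE could not be applied was managed without apnoeic oxygen, which is also how standard care is described. The sentence does not say whether such an encounter counts as standard care commenced (a crossover) or as nothing commenced (dropped). The attrition allowance is 960 − 816 = 144 encounters. It mixes non-delivery with missing outcomes, so it is at most an upper planning figure for either.

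**4. Illustration.** Assumed, not from the SAP: 20% of encounters are high-risk with 40% hypoxaemia; a share c of one arm switches, all of them high-risk; treatment has no effect. From the SAP: 16% overall. The low-risk rate is then (0.16 − 0.20 × 0.40) / 0.80 = 0.10.

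If THRIVE-allocated encounters are managed without it:
- as-treated: standard care = (0.16 + 0.40c) / (1 + c); THRIVE = (0.16 − 0.40c) / (1 − c)
- limited to allocated therapy received: standard care = 0.16; THRIVE = (0.16 − 0.40c) / (1 − c)

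At c = 0.10, as-treated: standard care 0.20 / 1.10 = 18.2%; THRIVE 0.12 / 0.90 = 13.3%; odds ratio 0.1538 / 0.2222 = 0.69. If standard-care encounters switch to THRIVE instead, the two rates swap and the odds ratio inverts.

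| c | As-treated OR, THRIVE not delivered | As-treated OR, standard care to THRIVE | Allocated therapy received OR, THRIVE not delivered | Allocated therapy received OR, standard care to THRIVE |
|---|---|---|---|---|
| 5% | 0.84 | 1.20 | 0.91 | 1.10 |
| 10% | 0.69 | 1.44 | 0.81 | 1.24 |
| 15% | 0.56 | 1.77 | 0.70 | 1.43 |

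The ITT odds ratio is 1.00 in every row. The allocation reading also gives 1.00 if no encounter is dropped.

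**5. With the planned halving of risk.** Take c = 0.10, with THRIVE not delivered. ITT: THRIVE = 0.5 × (0.10 × 0.40 + 0.80 × 0.10) + 0.10 × 0.40 = 10.0%, against 16.0% (OR 0.58). As-treated: 0.06 / 0.90 = 6.7% against 18.2% (OR 0.32). Limited to allocated therapy received: 6.7% against 16.0% (OR 0.37). With complete delivery it would be 8% against 16% (OR 0.46), so both non-ITT sets overstate the benefit here, the as-treated one more.

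**The case against.** The strongest defence is that little depends on this analysis. ITT is primary and clearly defined, the second analysis goes to the supplement, and no alpha, sample size or decision rule uses it. That stands, and it sets the severity.

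It is also fair to say that a conventional per-protocol set is no cure. Removing switchers selects after randomisation, and under no true effect the illustration still moves to 0.70 or 1.43. So the fault is a wrong label and an open grouping; a correct set would not be unbiased either.

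Four stronger readings are tempting, and the article does not support them:
- *That grouping by allocation would nearly reproduce ITT.* The number of encounters with no therapy commenced is not given.
- *That commencing a therapy means nothing for standard care.* The Intervention section describes standard care as a strategy that is carried out, so commencement can be read as intubation begun under it. The trigger is imprecise, not empty.
- *That the set changes the unit of analysis because it speaks of attempts.* The same section says "The unit of analysis for most outcomes is the intubation encounter" and uses attempt loosely for an enrolment. This is mostly terminology.
- *That the bias has a known size or direction.* No crossover rate is given. The only mechanism described is failure to deliver the intervention; switching from standard care to THRIVE is an assumption.

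**Conclusion.** The point holds at moderate severity. As written, the analysis is either a non-randomised as-treated comparison open to confounding or a modified ITT analysis, and the label fits neither. The supplementary results would be mislabelled, including the per-protocol version of the admission-level outcomes. A reader might infer that the main analysis of those outcomes, or the primary result, is compromised. It is not: both follow allocation, and this set does not enter them.

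The conclusion rests on the wording alone. The odds ratios (0.56 to 0.84, or 1.20 to 1.77, where the truth is 1.00) rest on the assumed 20% high-risk share, 40% risk and 5% to 15% switching. They show that the grouping can matter and do not predict what this trial will find.

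**What to change.** Define the per-protocol set as encounters that received the allocated strategy at the first attempt. In the THRIVE arm that means THRIVE applied before laryngoscope insertion, as the Intervention section already describes; in the standard-care arm it means no apnoeic oxygen. Analyse by allocated arm with the encounter as unit. State beside the result that the set is smaller than ITT and open to post-randomisation selection bias.

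If the present set is kept, rename it as-treated (and call it non-randomised) or modified ITT, state the grouping, and say how an encounter with undelivered THRIVE is classified.

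Either way, settle this before results by arm are seen and declare it as a change to the published SAP. The cost is a few sentences and one derived flag. The Data monitoring section already requires record and video review of every enrolled patient for protocol deviations. The drawbacks of the restricted set are lost encounters and the selection bias just named.
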